## Rationale for choice of primary endpoint

The aim of any local therapy is to maximise local control whilst minimising toxicity and any impact on functional reserve. This study is powered to detect a clinically relevant improvement in the primary endpoint of 2 year freedom from local progression (FFLP) with progression free survival (PFS), overall survival (OS), toxicity and patient reported outcomes representing important secondary endpoints. Whilst overall survival is considered the most robust efficacy endpoint for an intervention it can be confounded by the multitude of effective downstream therapies available and their subsequent effects on progression of tumour and underlying liver dysfunction.(43, 44) This is particularly the case when evaluating therapies in early stage HCC. For HCC multiple sequential local therapies are often employed whilst the disease remains in an early stage and hence, the trial investigators consider it impractical to limit post-progression therapy, including the option of cross-over therapy in the event of local or other intra-hepatic progression. Demonstration of a significant improvement in local control without increased toxicity within the context of a randomised trial would provide evidence to support the inclusion of SABR as an initial treatment option for single HCC (BCLC-O/A).

## Challenges in response assessment in hepatocellular carcinoma and across modalities.

Assessment of response and progression poses a number of challenges in the setting of local therapies for early stage HCC.(43, 44) For so called “typical” lesions that display intratumoural (non-rim like) arterial enhancement, complete necrosis of the tumour (as evidenced by a lack of arterial enhancement) following local therapies may be scored as stable disease (SD) via RECIST v1.1 or even progressive disease (PD) if cystic swelling of the necrotic lesion occurs. For thermal ablation, the post-ablation cavity is typically larger than the baseline RECIST v1.1 tumour measurement. Furthermore, the presence of regenerative nodules, post-therapy perfusional changes, ascites, pleural effusions and enlarged peri-portal lymph nodes can all occur in the context of underlying cirrhosis and/or prior therapies in the absence of true disease progression. The modified RECIST (mRECIST) criteria were developed to address the above issues and reduce the overreporting of progressive disease. (43)

mRECIST takes into account the events that can be attributable to the natural history of cirrhosis as above and also introduced the concept of “viable” tumour for response assessment of target lesions. It defines “typical” intrahepatic HCC lesions as ones that demonstrate intratumoural (*i.e.* non-rim-like) arterial enhancement on contrast-enhanced CT or MRI. For typical lesions mRECIST recommends measuring the longest diameter of viable tumour (i.e. any persistent enhancement) instead of overall lesion diameter. Target lesion progression using mRECIST criteria requires at least a 20% increase (compared to nadir) in longest diameter of viable arterial enhancing tumour with an absolute increase of ≥5mm. This measurement should exclude intervening areas of complete necrosis. A new typical intrahepatic lesion must be ≥1cm. This has been shown to be a more accurate predictor of response and progression for typical lesions treated with thermal ablation or TACE. (43)

“Atypical” intrahepatic lesions are defined in mRECIST as non-enhancing or rim enhancing lesions. These features can be seen in well differentiated, steatotic or poorly differentiated tumours and have often undergone biopsy confirmation. For these lesions RECIST v1.1 criteria, i.e. overall tumour diameter measurements, should apply. A new atypical intrahepatic lesion is regarded as equivocal until interval growth ≥10mm is demonstrated on subsequent scans.

Whilst mRECIST has advantages for response assessment in the setting of thermal ablation, TACE and some systemic therapies, the distinct mechanism of action of radiation-based therapies introduces further challenges. For radiation-based therapies such as radio-embolisation and SABR, both persistent arterial phase hyperenhancement within the target lesion and geographic arterial phase hyperenhancement without washout in the adjacent parenchyma are common in the first 3-12 months following treatment.(45) In contrast to thermal ablation or TACE, residual enhancement in this period is not predictive of subsequent local progression. (46)

The distinct natural progression of target lesion and adjacent parenchymal changes following SABR has been illustrated by Mendiratta-Lala and colleagues.(46) In the first 3 to 12 months following SABR, the arterial phase hyperenhancement gradually converts to portal venous and delayed phase hyperenhancement, as radiation induced veno-occlusion and fibrosis develops, with overlying capsular retraction. Lack of washout or other features such as diffusion restriction can help differentiate expected post-radiation perfusional changes from infiltrative tumour. Radiation-induced biliary strictures, and their associated distal segmental changes, can develop after SABR for more central tumours. Despite mRECIST response having a lower predictive ability in the early months following SABR, with the majority demonstrating stable disease, subsequent new nodular or increasing volume and intensity of arterial phase hyperenhancement with washout are indicators of progressive disease.

Despite the above challenges in assigning various categories for response such as stable disease, partial or complete response, the endpoint of progressive disease appears to be more reliable. The primary endpoint of the SOCRATES study will be FFLP with local progression defined as target lesion progression as per mRECIST criteria (viable tumour diameter for typical lesions, lesion diameter for atypical lesions). Given the potential for more complex vascular changes following radiation-based therapies, RECIST v1.1 measurements will also be taken and local progression events will also include progression on RECIST v1.1. criteria. For the thermal ablation cohort, the post-ablation cavity will serve as baseline for RECIST v1.1 measurements. Central, independent radiological review will be undertaken for progression events with equivocal findings or non-consensus regarding progression requiring interval imaging to confirm progression (backdated to the previous imaging time point).

## Patient reported outcomes

Given the increasing number of therapies available for early stage HCC, evaluation of patient reported outcomes (PROs) can provide valuable additional insights into the relative tolerability profile of these therapies. A scoping review of PROs in HCC by the American Association for the Study of Liver Diseases (AASLD) has highlighted a paucity of high-quality data, in particular for locoregional therapies (TACE/TARE) and radiotherapy in HCC. (47) The majority of studies to date have consisted of small, single-centre cohorts.The European Organization for Research and Treatment of Cancer (EORTC) Quality of Life Questionnaire (EORTC QLQ-C30) is a well validated general PRO measure and will provide valuable information on general health related quality of life (HRQoL) and health utility across the treatments.(48) In addition, the EORTC QLQ-C30 can also be used to assess quality of life weights for inclusion in assessments of relative treatment value as part of cost-effectiveness analyses(49). The EORTC Hepatocellular Carcinoma 18-question module (EORTC QLQ-HCC18) was developed specifically to assess symptom burden and impact on HRQoL in people with HCC. (50) It has been validated previously in advanced and pre-treated, unresectable HCC cohorts with estimates of meaningful within patient changes developed.(51) However, data specifically on first line therapy for early stage HCC and in particular comparisons between SABR and current first-line therapies are lacking.

## The SOCRATES Trial

Despite encouraging randomised and non-randomised data and it’s increasing use in a number of centres around Australia, SABR is currently not recommended as a first-line therapy option for early-stage HCC in most HCC guidelines owing to a lack of randomised studies. (5, 6, 52) High-quality randomised controlled trials of SABR in patients with early-stage HCC who are non-surgical candidates, are important to compare efficacy, toxicity, patient acceptability and cost-effectiveness with the current SOC. The SOCRATES randomised controlled trial will assess the efficacy, toxicity, HRQoL profile and cost effectiveness of SABR compared to the current SOC treatment in patients with first diagnosis of unresectable, single nodule HCC.

# TRIAL OBJECTIVES

## Research Hypothesis

SABR will result in higher rates of FFLP at 2 years compared to percutaneous thermal ablation ± TACE or transarterial therapies (TACE/TARE).

## Objectives

**Table 2: Objectives and Endpoints**

|  | **OBJECTIVE** | **ENDPOINT** |
| --- | --- | --- |
| **PRIMARY** | Evaluate the efficacy of SABR compared to SOC first line therapies in terms of local lesion control | 2-year FFLP according to mRECIST ( or RECIST v1.1 when mRECIST can’t be used) |
| **SECONDARY** | Evaluate progression-free survival | 2-year PFS |
|  | Evaluate overall survival | 2-year OS |
|  | Evaluate safety and adverse events | Cumulative incidence of adverse events (CTCAE v5) |
|  | Compare patient reported outcomes between SABR and SOC therapies | EORTC QLQ-C30 and QLQ-HCC18 - mean scores over time. Time to ≥10 point decrease in the combined GHS/QoL score. |
|  | Cost-effectiveness analysis | Incremental cost per outcome (additional patient with FFLP at 2 years; and quality adjusted life years) for SABR compared with SoC. |
|  | Qualitative review of patient experience | Patient treatment experience assessed by qualitative methods |
| **EXPLORATORY** | To identify biomarkers associated with treatment outcome. | Changes in serum AFP, haematological and liver function parameters post-treatment. |

# TRIAL DESIGN

The study is designed as a phase II, prospective, randomised, parallel and open-label, multi-institutional superiority trial for patients with newly diagnosed early stage (BCLC 0/A) , solitary ≤8cm nodule HCC, ineligible for surgical resection or transplantation.

Patients with tumours ≤ 3cm **and** eligible percutaneous thermal ablation will be randomly assigned (1:1 ratio) to either thermal ablation or SABR.

Patients with tumours ≤ 3cm assessed as ineligible for thermal ablation or patients with tumours >3cm will be randomly assigned (1:1 ratio) to either SABR or standard of care which can include transarterial therapies (TACE or TARE) and or percutaneous thermal ablation (MWA or RFA). See **Figure 1: Study Schema.**

# PARTICIPANT SELECTION AND ELIGIBILITY

## Target population

The target population includes any newly diagnosed, early stage (BCLC 0/A) HCC with solitary ≤8 cm nodule, ineligible for or declined liver resection, not planned for transplantation and with clinically compensated cirrhosis (Child-Pugh score ≤B7).

## Accrual numbers and timelines

Target accrual is 118 participants for Cohort 1 and 100 for Cohort 2. Participant enrolment is anticipated to take 2 years. The total duration of this study with assigned treatment and follow-up is estimated to be around 5 years, which includes obtaining ethics and governance approvals (6 months), recruitment (2 years), follow-up of all patients (2 years per patient) and completion of data collection and analysis (6 months)

## Eligibility Criteria

Patients must meet all of the inclusion criteria and none of the exclusion criteria to be eligible for this trial. **It is important that there will be no exceptions (exemptions or waivers) made to these eligibility requirements at the time of enrolment**.

All enquiries about eligibility should be addressed as soon as possible and prior to enrolment by contacting [[contact]](mailto:[contact]).

### Inclusion criteria

1. Histological or radiological diagnosis of single, new HCC with largest diameter ≤8 cm (BCLC^[[1]](#footnote-2)^ stage 0 or A).
   1. If prior history of HCC, the prior HCC must have been:
      - Early stage, solitary HCC, ≤5 cm in size **and**,
      - Have arisen within a different liver segment to the current HCC **and,**
      - Treated with curative intent therapy >2 years prior with no evidence of activedisease at the site.
2. As per local multidisciplinary HCC meeting consensus patient is suitable for percutaneous thermal ablation and/or transarterial therapies **and** not suitable for or declined liver resection **and** not planned for liver transplantation.
3. Child-Pugh score ≤B7^*^ with no or diuretic-controlled ascites
4. ECOG performance status ≤2^[[2]](#footnote-3)^
5. Platelets ≥50x10^9^/L, Haemoglobin ≥80 g/L, Neutrophils ≥1.0x10^9^/L, INR <1.8 (except if on therapeutic anticoagulation)
6. 18 years of age or older and able to provide written consent

### Exclusion criteria

1. Presence of multifocal HCC, macrovascular invasion or extrahepatic disease
2. Prior treatment for any HCC within last 2 years.
3. Clinically evident ascites or hepatic encephalopathy
4. Prior abdominal radiation therapy that would preclude the delivery of protocol defined SABR to the tumour.
5. Untreated Hepatitis B or C
6. Known additional invasive malignancy (excluding non-melanoma skin cancer) that is progressing or required treatment within the last 2 years.
7. Pregnancy

# SCREENING

## Screening Log

Appropriately qualified personnel at the Trial Site will screen patient health records for potentially suitable patients according to the eligibility criteria in the protocol. The Trial Site will then record de-identified information relating to each patient screened on the screening log (including in-eligible patients); screening will continue until the target population is achieved. The screening log will be requested by the Trial Coordinating Centre on a regular basis for the purpose of monitoring accrual.

## Informed Consent

Patients must be given the current ethically approved participant information sheet for their consideration. Patients should only be asked to consent to the study after they have had sufficient time to consider the trial and the opportunity to ask any further questions. Any study specific procedures can only be performed after the participants has consented to participate.

Patients will also be asked to separately consent to the study team accessing their Medicare data for PBS and MBS funded health care service use.

## Participation in other research

Enrolment of a participant into another treatment intervention study is not permitted prior to confirmed disease progression.

Enrolment in unrelated non-interventional studies is discouraged but will be considered on a case by case basis by the Trial Management Committee. Any study that could impact on the primary endpoint of the SOCRATES study is not permitted.

## Methods for assigning treatment groups

The appropriate delegated staff member will determine the patients eligibility (see Section 4.3 Eligibility Criteria) prior to randomisation.

### Cohort selection

Each participant will be allocated into a cohort based on the following criteria;

- Patients with HCC ≤ 3 cm deemed **eligible** for percutaneous thermal ablation by the local MDT^[[3]](#footnote-4)^ will be allocated to Cohort 1
- Patients with HCC >3cm or deemed **ineligible** for percutaneous thermal ablation by the local MDT will be allocated to Cohort 2

### Randomisation Treatment Allocation

Participant will be randomised within each cohort;

- Participants in Cohort 1 will be randomly allocated (1:1) to receive either SABR verses percutaneous thermal ablation.
- Participants in Cohort 2 will be randomly allocated (1:1) to receive SABR verses SOC therapies
  *Note: SOC therapies include transarterial therapies (TACE or TARE) and/or MWA/RFA (alone or in combination).*

All randomisations will be completed through a web-based, password-protected randomisation system. Once the investigator has confirmed eligibility, the randomisation details are to be entered into the system by suitably delegated site personnel. The eligibility criteria will be reviewed by trial management staff prior to randomsiation. A confirmation of randomisation and treatment allocation will be emailed to site personnel, including the principal investigator.

Randomisation for both cohorts will be performed using block sizes of 4 to help ensure minimal imbalance in the size of treatment groups for each cohort.

Participants in each cohort will be stratified for;

1. Child-Pugh classification (A vs. B7)
2. BCLC stage (0 vs. A ; i.e. maximum tumour diameter ≤2 cm vs. >2cm)

Participants can only be randomised once in this trial.

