## Blinding

Participant and treating clinicians will not be blinded to the treatment assignment after the randomisation process. Given the distinct post-treatment imaging appearances of the different therapies it is also not feasible to reliably blind the local radiologists or central independent radiological review to treatment assignment.

Data collectors and analysers will be blinded to treatment assignment

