## Sequence Generation

Randomisation for both patient groups will be performed using random block sizes of 6 and 4 to help ensure minimal imbalance in the size of treatment groups for each patient cohort.

To prevent imbalance in disease severity and HCC BCLC stage, stratified block randomisation using two factors will be used for SABR vs SOC cohorts (see **Section 5.4.2 Randomisation Treatment Allocation**).

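### Sections 5.4.2 and 14.2 give different block sizes for the same randomisation, and both print the sizes in a protocol held by sites in an open-label trial

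*Protocol*

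**What the plan says.** Protocol Section 5.4.2 (Randomisation Treatment Allocation) states: "Randomisation for both cohorts will be performed using block sizes of 4 to help ensure minimal imbalance". It names no second size and does not mention random variation. Protocol Section 14.2 (Sequence Generation) states: "Randomisation for both patient groups will be performed using random block sizes of 6 and 4 to help ensure minimal imbalance". It adds that "stratified block randomisation using two factors will be used for SABR vs SOC cohorts" and points to Section 5.4.2 for the detail.

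The rest of the scheme is consistent. Allocation is 1:1 in each cohort: "Participants in Cohort 1 will be randomly allocated (1:1) to receive either SABR verses percutaneous thermal ablation" and "Participants in Cohort 2 will be randomly allocated (1:1) to receive SABR verses SOC therapies". Each cohort is stratified by Child-Pugh class (A or B7) and BCLC stage (0 or A), which gives four strata per cohort. Site is not listed as a factor. Randomisation runs through a central web system, and each result is emailed to site staff, including the principal investigator.

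On blinding, Section 5.5 says: "Participant and treating clinicians will not be blinded to the treatment assignment after the randomisation process". It adds that radiological review cannot be reliably blinded either.

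**The concern.** The two sentences describe one procedure for the same patients with the same stated purpose, yet they specify different procedures. Neither belongs to a change log; both are current text. From this protocol nobody can tell which list the web system was built from, and the final report could not describe the allocation method from it.

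The difference bears on allocation concealment. The trial is open label and sites receive each allocation by email, so a site builds up its own allocation history. If the block size is known and constant, the end of each block can be deduced by anyone who has followed the stratum from its start. A person who knows or suspects the next assignment can influence whom to approach, and when. Entry to a cohort depends partly on the local multidisciplinary meeting's view of suitability for ablation. Bias from selective enrolment would fall on the primary comparison and could not be reliably removed in the analysis. With outcome review also unblinded, concealed allocation is one of the few protections left.

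**Working it through.** **The protocol's own figures.** No sample size, power or error rate depends on block size, so there is no stated number to reproduce. The contradiction is established by comparing the two sections: 4 only in Section 5.4.2; 4 and 6 at random in Section 14.2.

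**Inputs from the protocol.** 1:1 allocation; four strata per cohort; open label; site not a stratification factor; targets of 118 and 100 (Section 4.2). The mean stratum size is therefore 118/4 = 29.5 in Cohort 1 and 100/4 = 25 in Cohort 2.

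**Inputs not in the protocol (assumed).** Blocks of 4 and 6 equally likely; 30 patients per stratum and 1 to 15 equal sites for the single-site calculation.

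**Step 1: observer who sees the whole stratum, fixed block of 4.** There are 6 possible blocks, or 6 × 4 = 24 positions. AABB and BBAA each force their last two positions; the other four blocks force only the last.

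- Forced share: (2 × 2 + 4 × 1)/24 = 8/24 = 33.3%.
- Correct guesses when always choosing the arm with more places left: position 1, 1/2; position 2, 2/3; position 3, (1/3 × 1) + (2/3 × 1/2) = 2/3; position 4, 1. The mean is (0.500 + 0.667 + 0.667 + 1)/4 = 70.8%.

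The same enumeration for a fixed block of 6 gives 25% forced and 68.3% guessed correctly.

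**Step 2: the same observer, random 4 and 6.** The observer knows the possible sizes but not their order, and updates after each allocation (20,000 simulated sequences for each length).

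| Allocations in stratum | Certain | Guessed correctly |
|---|---|---|
| 12 | 6.3% | 68.0% |
| 24 | 5.8% | 68.6% |
| 30 | 5.8% | 68.8% |
| 60 | 5.6% | 69.1% |

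Certain knowledge falls from 33.3% to about 6%. The overall guess rate falls only from 70.8% to about 68-69%.

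**Step 3: observer who sees only one site's patients.** The observer guesses the arm that is behind at that site within the stratum (20,000 sequences of 30). A correct-guess rate of 50% is chance.

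| Equal sites | Fixed 4 | Random 4 and 6 |
|---|---|---|
| 1 | 70.0% | 68.8% |
| 2 | 55.3% | 55.4% |
| 5 | 52.7% | 52.7% |
| 10 | 51.5% | 51.6% |
| 15 | 51.2% | 51.0% |

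The one-site value under fixed 4 is 70.0% rather than 70.8% because 30 is not a multiple of 4. From 2 sites upwards the gain over chance is about 1 to 5 points, and the schemes differ by at most 0.2 points.

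**The case against.** The strongest reply is that the contradiction is real but its practical effect is small. A reader might infer from the one-in-three figure that sites can generally guess allocations. The documents do not support that. The trial is multi-institutional, site is not a listed stratification factor, and nothing says that a site sees other sites' allocations. Under those conditions Step 3 applies, and neither scheme gives a site much. This part of the reply stands.

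Three further inferences also go too far:

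- **That a fixed block of 4 was implemented.** Section 5.4.2 does not use the word fixed. Section 14.2 is the dedicated section and says random. An incomplete summary in Section 5.4.2 is a plausible explanation.
- **That disclosure harms only the Section 5.4.2 version.** Section 14.2 prints its sizes in the same protocol.
- **That the strata are small throughout.** No stratum sizes are given and the means are 29.5 and 25. They are probably uneven: every Cohort 2 tumour above 3 cm falls in the larger-diameter stratum. What drives predictability is one site's share of a stratum.

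The protocol also has safeguards. Trial management staff review eligibility before randomisation, the sponsor reviews it for all participants, screening logs include ineligible patients, waivers are ruled out, and the multidisciplinary team has a minimum membership. These limit selective enrolment. They do not control whom a site offers the trial or when, and they do not settle which block scheme is correct.

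**Conclusion.** The point holds as an inconsistency that touches allocation concealment. The two sections conflict, and both publish the block sizes to unblinded sites.

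The choice of scheme makes a clear difference only to someone who sees a whole stratum: one allocation in three certain under a known block of 4, against about 6% under random 4 and 6. That comparison assumes that the two sizes are equally likely. For a site that sees only its own patients the gain is about 1 to 5 points over chance under either scheme, assuming 2 to 15 equal sites, 30 patients per stratum and a simple guessing rule. The protocol does not give the number of sites. The exposure therefore lies mainly where one site supplies most of a stratum, or where allocations are shared between sites.

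Nothing in the document shows that bias has occurred. The correction should still be made, because it is cheap and the method of allocation has to be reported accurately.

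**What to change.** 1. Confirm from the web system which scheme it runs.
2. Make Section 5.4.2 agree with Section 14.2. Both should state only that stratified permuted blocks of randomly varying size are used, provided that step 1 shows this to be true of the system.
3. Remove the sizes from the site-facing protocol and hold them in a randomisation document with restricted access.
4. Report the scheme actually used, including any change during recruitment.

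If the system runs random sizes, the cost is wording alone. If a fixed block of 4 was implemented, varying the sizes for the remaining allocations is optional, since Step 3 shows little gain for a site among several. It would mean regenerating the unused part of the lists and accepting a slightly larger possible imbalance: at most 3 rather than 2 within a stratum, hence at most 4 × 3 = 12 rather than 4 × 2 = 8 across a cohort's four strata. If the fixed block is kept, the protocol should say only that stratified permuted blocks are used. Removing the sizes now does not undo their disclosure to sites that already hold this version.
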